## Abstract

**Background:**

People with Parkinson's disease are twice as likely to be recurrent fallers compared to other older people. As these falls have devastating consequences, there is an urgent need to identify and test innovative interventions with the potential to reduce falls in people with Parkinson's disease. The main objective of this randomised controlled trial is to determine whether fall rates can be reduced in people with Parkinson's disease using exercise targeting three potentially remediable risk factors for falls (reduced balance, reduced leg muscle strength and freezing of gait). In addition we will establish the cost effectiveness of the exercise program from the health provider's perspective.

**Methods/Design:**

230 community-dwelling participants with idiopathic Parkinson's disease will be recruited. Eligible participants will also have a history of falls or be identified as being at risk of falls on assessment. Participants will be randomly allocated to a usual-care control group or an intervention group which will undertake weight-bearing balance and strengthening exercises and use cueing strategies to address freezing of gait. The intervention group will choose between the home-based or support group-based mode of the program. Participants in both groups will receive standardized falls prevention advice. The primary outcome measure will be fall rates. Participants will record falls and medical interventions in a diary for the duration of the 6-month intervention period. Secondary measures include the Parkinson's Disease Falls Risk Score, maximal leg muscle strength, standing balance, the Short Physical Performance Battery, freezing of gait, health and well being, habitual physical activity and positive and negative affect schedule.

**Discussion:**

No adequately powered studies have investigated exercise interventions aimed at reducing falls in people with Parkinson's disease. This trial will determine the effectiveness of the exercise intervention in reducing falls and its cost effectiveness. This pragmatic program, if found to be effective, has the potential to be implemented within existing community services.

**Trial registration:**

The protocol for this study is registered with the Australian New Zealand Clinical Trials Registry (ACTRN12608000303347).

## Background

The number of persons with Parkinson's disease over age 50 in Western Europe's five most populous nations was up to 4.6 million in 2005, and this will double to up to 9.3 million by 2030 [1]. Over 100,000 Australians are currently living with Parkinson's disease [2] and in line with estimates from Western Europe this number is also expected to double by 2030 [1]. Since the most common age of onset is 50–60 years and life expectancy is near normal, people with Parkinson's disease suffer the debilitating consequences of the disease over decades.

The mainstay of medical treatment for Parkinson's disease is pharmacological therapy to boost depleted dopamine levels. Despite optimal medication, people with Parkinson's disease living in the community experience frequent and recurrent falls with devastating consequences. Up to 68% of people with Parkinson's disease will fall and up to 46% of people with Parkinson's disease will experience recurrent falls each year [3-6]. These rates are around twice of those in the general older population [6]. In addition, a 12-month prospective study (n = 113) found that 27% of people with Parkinson's disease fell at least once each month and 15% fell at least once a week [3].

Among people with Parkinson disease, as many as 65% of fallers will experience an injury secondary to their falls, 33% will suffer a fracture and 75% of falls will lead to use of a health care service [7]. Falls and related fractures are the most common secondary reason that people with Parkinson's disease are admitted to hospital [8]. These falls have devastating consequences and are accompanied by pain, reduced mobility and unacceptably high levels of caregiver stress. Fear of falling is also greater in community-dwelling people with Parkinson's disease than healthy controls [9]. This results in restriction of activities, compromising quality of life and predisposing to secondary reductions in muscle strength and cardiovascular fitness.

Recently Latt (2006) tested a battery of physiological and clinical variables considered to be potential risk factors for falls in people with Parkinson's disease [3]. These included Parkinson's specific impairments, such as slowness of movement, poor balance, freezing of gait and cognitive impairment as well as age-related impairments, such as reduced lower limb muscle strength. After adjusting for past falls, it was found that freezing of gait, poor balance and lower limb muscle weakness were independent predictors of falls. Therefore, the logical targets for an exercise program designed to reduce falls would be freezing of gait, balance and lower limb muscle strength.

Systematic reviews in the general older population, have found that exercise programs which specifically target balance and lower limb muscle strength are effective in preventing falls [10,11]. In people with Parkinson's disease, lower limb muscle strength and regular exercise are significantly correlated with physical abilities [12-15], therefore highlighting the role of exercise as an appropriate intervention in this population. Exercise has been shown to improve balance [16-18] and strength [18,19] and cueing training [20] has been shown to improve freezing of gait [17] in people with Parkinson's disease. However, no previous randomised controlled trials have investigated an exercise intervention aimed at reducing falls in people with Parkinson's disease by simultaneously targeting all three of these predictors of falls. The Weight-bearing Exercise for Better Balance (WEBB) exercise program has been developed to specifically target poor balance and lower limb muscle weakness for people at risk of falls. The PD-WEBB program used in this study includes progressive weight-bearing balance and strength exercises along with evidence-based cueing strategies to address freezing of gait. (The PD-WEBB program is available from the authors on request).

The primary aim of this randomised controlled trial is to determine the effectiveness of the PD-WEBB exercise program in reducing the rate of falls in people with Parkinson's disease. In addition, we will establish the cost effectiveness of the program from the health provider's perspective and determine the effects of the program on i) risk factors for falls, ii) physical abilities, iii) fear of falling and iv) quality of life.

## Methods

### Design

A prospective, randomised controlled trial will be conducted with 230 community-dwelling participants with Parkinson's disease (Figure 1).

**Figure 1 F1:**
[figure not shown]
**Trial design**.

### Participant selection

To be included in the study participants must meet the following inclusion criteria: (i) a diagnosis of idiopathic Parkinson's disease; (ii) aged 40 years or over; (iii) able to walk independently with or without a walking frame; (iv) fallen at least once in the past 12 months or found to be at risk of falls on assessment; (v) have adapted to their current anti-Parkinsonian medication for at least 2 weeks.

Participants will be excluded if they have a Mini-Mental State Examination score of < 24, or suffer from unstable cardiovascular disease, or suffer from other uncontrolled chronic conditions that would interfere with the safety and conduct of the training and testing protocol or interpretation of the results.

All volunteers will be screened by a physiotherapist. Medical clearance will be required from each participant's medical practitioner to certify him/her as able to participate in moderate-intensity semi-supervised exercise before being accepted into the trial.

The study protocol has been approved by The University of Sydney Human Research Ethics Committee (HREC Number 11-2007/10487), and Sydney West Area Health Service Human Research Ethics Committee (HREC2008/9/4.13 (2865) AU RED 08/WMEAD/250) and written informed consent will be obtained from all participants.

### Measurements and Procedures

All participants will undergo two measurements: one on entry to the study (pre-test) and one after the 6-month intervention period (post-test). All pre-test measures will be assessed prior to randomisation. Cognitive function will be assessed with the Mini Mental State Examination [21]. Measurements will be conducted one hour after each participant's last dose of L-dopa, thus each participant will be tested in their "on" phase.

### Intervention Group

#### Program

The intervention group will undertake the PD-WEBB program. This includes a 40–60 min program of progressive balance and lower limb strengthening exercises 3 times a week for 6 months as well as evidence-based cueing strategies to reduce freezing of gait [20]. Participants will have the option to participate in a *support group*-*based *program in which they attend monthly exercise classes conducted by a physiotherapist as well as perform the exercises at home. If they choose this option, the exercises will be updated by the physiotherapist at the class and they will receive two to four home visits by the physiotherapist over the 6 months to ensure that the exercises are performed safely and effectively at home. Participants who choose the *home-based *mode will have eight to ten sessions supervised and progressed by a physiotherapist over the 6 months. These participants will carry out the other sessions independently, following specific written and pictorial instructions provided by the physiotherapist.

#### Exercises

All exercise sessions will include 5 minutes warm-up exercises. The lower limb extensor muscle groups, which act to prevent collapse of the lower limb (hip and knee extensors and ankle plantarflexors) will be targeted with exercises designed to enhance postural control (i. e. balance) and muscle strength. The balance exercises include standing with a decreased base of support, forwards and sideways stepping/walking, and graded reaching activities in standing. Strengthening exercises will include sit-to-stand, forward or lateral step-ups onto a small block, semi squats and heel raises in standing. Resistance for strengthening exercises will be applied using weighted vests in a similar protocol to one which has been successfully used by people with multiple sclerosis in a home-based program [22]. Standard principles governing frequency, volume, duration, intensity and progression of exercise will be applied [23]. Cueing strategies will be used to reduce freezing [17,20,24]. These include identifying appropriate methods of cueing (cognitive, auditory, somatosensory) for each participant and incorporating these cues into everyday activities.

#### Safety

Participants will be instructed how to perform exercises safely with stable supports (such as a table) located nearby for additional support if required. Maintaining safety while exercising will be a prime consideration when level of difficulty of exercises is prescribed and progressed. Participants will be provided with a booklet containing safety precautions, instructions and photographs of exercises for use in exercise sessions at home. In addition, they will be provided with a logbook for recording exercises completed and effects of exercise (e.g. muscle soreness). Any participant who does not demonstrate safety in the independent performance of their exercises after two home visits will be withdrawn from the study. Where appropriate, family members and/or carers, will be encouraged to assist with supervision and performance of the exercise program.

The intervention group will also receive standardised falls prevention advice in the form of a booklet.

### Control group

The control group will receive their usual care from their medical practitioner and community services. In addition, standardised falls prevention advice in the form of a booklet will be provided.

### Outcome measures

The primary outcome measure will be falls:

*Falls *will be assessed by comparing the number of falls in intervention and control groups. The proportion of fallers in each group will also be compared. Falls will be recorded by the use of a "falls diary". All participants will receive monthly calendars on entry to the study, with instructions to record the following events: number of falls, visits by or to nursing and allied health personnel, general practitioner or specialists appointments and hospitalisations. Participants will be asked to return the completed calendar monthly in pre-paid envelopes to the research personnel who are unaware of group allocation. All participants will also be telephoned monthly to record any changes in medications, use of health resources and verify any falls details (including how and where the fall occurred, injuries suffered, medical intervention required and limitations to activity as a result of a fall).

To evaluate the cost effectiveness of the exercise program the following measures will be collected:

*Costs of the intervention: *the costs of implementing the exercise program will be obtained from trial records and research group financial records using actual costs when available. Costs associated with developing and evaluating the exercise program will be excluded from the analysis.

*Costs of health services used for managing fall-related injuries*: use of public and private healthcare resources will be recorded as part of the monthly telephone calls, over the 6-month intervention period.

The secondary outcome measures listed below will be collected on entry to the study and at the end of the 6-month intervention period by an assessor unaware of group allocation. The order of measurements will be standardized. Participants will be instructed not to inform the assessors of their intervention status, and all home exercise equipment will be removed or concealed prior to the post-assessment.

Secondary outcome measures are:

(i) *Parkinson's Disease Falls Risk Score: *Falls risk status will be determined using the Parkinson's disease-specific algorithm developed in our recent large prospective cohort study [3]. This involves weighted contributions from neurological and physiological function measures including gait freezing, impaired balance and lower limb weakness.

(ii) *Maximal muscle strength *of the knee extensor muscles of each leg will be tested using a strain gauge [25].

(iii) *Balance in standing*, using the coordinated stability test which requires participants to accurately adjust their position in a steady and coordinated manner when their centre of mass is near the limits of their base of support [26].

(iv) *Short Physical Performance Battery*, including tests of walking, balanced standing and sit to stand [27].

(v) *Freezing of gait*, using the Freezing of Gait Questionnaire [28].

(vi) *Falls Efficacy Scale International*, a falls efficacy questionnaire [29].

(vii) *Health and Well-being*, using the SF12v2™.

(viii) *Habitual Physical Activity Questionnaire *to quantify the type and amount of regular physical activity.

(ix) *PDQ-39*, a Parkinson's disease specific quality of life questionnaire [30].

(x)* Positive and Negative Affect*, using the Positive and Negative Affect Schedule (PANAS) [31].

Adverse events (defined as a significant injury or medical event that causes the participant to seek attention from a health professional or limit their activities) will be monitored and recorded throughout the study during the monthly telephone calls to each participant.

### Statistical analysis

The number of falls per person-year will be analysed using negative binomial regression to estimate the difference in fall rates between the two groups, adjusted for previous multiple faller status and other confounding variables if required [32]. The proportion of fallers between groups will be compared using the relative risk statistic. Between-group comparisons of final test performance for the continuously-scored outcome measures will be made using General Linear Models (ANCOVA) controlled for pre-test performance. Baseline continuously-scored data will be compared between groups using the student t-test. Ordinally-scored data will be analysed for between group differences using the non-parametric Mann Whitney U statistic. An intention-to-treat approach will be used for all analyses.

Economic analysis will be undertaken in the manner used in previous falls prevention studies [33,34]. The total costs in intervention and control groups (including the cost of the exercise program, and costs of health and community service contacts) and falls rates, will be used to calculate an incremental cost per fall prevented in the intervention group compared with the control group. Bootstrapping will be used to estimate a distribution around costs and health outcomes and to calculate confidence intervals around the cost-effectiveness ratio; one-way sensitivity analyses will be conducted around key parameters.

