### Sample size

As fall rates will be compared between groups using incident rate ratios (IRR) from negative bionomial regression models [32] we conducted an analysis of statistical power using the nbpower command in the STATA software package. A total of 230 participants (115 per group) will be required to provide 80% power to detect as significant, at the 5% level, a 30% lower rate of falls for exercise subjects than control subjects (i. e. IRR = 0.70). We assumed the control group rate of falls would be 1 fall/person month over the 6-month follow-up period, a conservative estimate as the prospective cohort study [3] reported a falls rate of 1.6 falls/person month in a 12-month follow up of 113 people with PD.

The sample size of 230 will also be sufficient to detect between-group differences of 23% of control group values in the coordinated stability (balance) measure (assuming a control group mean of 18 and SD of 14) and 11% for knee extension strength (assuming a control group value of 16 kg and SD of 6). Both calculations are based on values found among fallers with PD [3] assuming 80% power of a two-sided test at the 5% level, a correlation between pre-and post measures of 0.7, and 15% dropouts.

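### The primary fall-rate model leaves the baseline Parkinson's Disease Falls Risk Score to an unstated criterion, so precision available from data already collected is not secured

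*Protocol article*

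**What the plan says.** The Statistical analysis section of the Protocol article compares fall rates by negative binomial regression, "adjusted for previous multiple faller status and other confounding variables if required". One covariate is therefore fixed. The others are not named, and nothing states what would make one required.

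Three other places bear on this:

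- **Background**, on the earlier cohort study: "After adjusting for past falls, it was found that freezing of gait, poor balance and lower limb muscle weakness were independent predictors of falls".
- **Outcome measures**, on the Parkinson's Disease Falls Risk Score, a secondary outcome collected at entry and at six months: "This involves weighted contributions from neurological and physiological function measures including gait freezing, impaired balance and lower limb weakness".
- **Measurements and Procedures**: "All pre-test measures will be assessed prior to randomisation".

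For the continuous secondary outcomes, the Statistical analysis section fixes an ANCOVA on the pre-test value. The baseline risk score is thus used when the score is itself the outcome. It has no assured place in the model for falls.

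**The concern.** In a randomised trial, confounding by a baseline variable can only mean chance imbalance. A clause that admits covariates as confounders when needed therefore invites a decision based on how the baseline data turn out. The benefit of adjusting for a prognostic variable does not depend on imbalance. It comes from explaining between-person variation in fall rate, which otherwise stays in the dispersion term and widens the interval for the rate ratio.

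By the protocol's own account, the three factors in the score carry information that fall history does not. The score is a proper baseline covariate and is already paid for. Two things are at stake: some precision on the primary question, and a primary estimate that does not depend on a covariate choice made after the baseline data are seen.

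**Working it through.** **Inputs (Protocol article, Sample size).**
- 115 per group: "A total of 230 participants (115 per group) will be required to provide 80% power".
- 5% level, with sides not stated for falls. Two-sided is assumed, as for the secondary measures: "assuming 80% power of a two-sided test at the 5% level".
- Effect: "a 30% lower rate of falls for exercise subjects than control subjects", a rate ratio of 0.70.
- Control rate of 1 fall per person-month over 6 months, so 6 expected falls in the control arm and 6 × 0.70 = 4.2 in the exercise arm.
- Not given: the dispersion k, and the partial correlation ρ between the score and the fall rate beyond fall history.

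**Step 1: the plan's own figure.** With the usual Wald approximation,

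SE(log IRR) = √[(1/6 + 1/4.2 + 2k)/115], and power = Φ(|ln 0.70|/SE − 1.96).

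Here 1/6 + 1/4.2 = 0.405 and |ln 0.70| = 0.357. Because k is not stated, the 230 cannot be reproduced independently. Setting power to 80% and solving gives k ≈ 0.73:
- variance term 0.405 + 1.459 = 1.864
- SE = √(1.864/115) = 0.127
- 0.357/0.127 = 2.80, so power is 80%.

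If the 115 already allows for the 15% dropout quoted for the secondary measures (97.75 analysed per arm), k ≈ 0.59.

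**Step 2: how much of the variance a covariate could reduce.** The share due to between-person heterogeneity is 1.459/1.864 = 78%. A prognostic covariate acts on this part.

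**Step 3: effect of adding the score.** Assume that 0.73 is the dispersion left after fall-history adjustment and that the score reduces it to 0.73 × (1 − ρ²):

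| Assumed ρ | Residual k | SE | Power | Per arm for 80% |
|---|---|---|---|---|
| 0 | 0.730 | 0.127 | 80% | 115 |
| 0.2 | 0.700 | 0.125 | 81% | 112 |
| 0.3 | 0.664 | 0.123 | 83% | 107 |
| 0.4 | 0.613 | 0.119 | 85% | 101 |
| 0.5 | 0.547 | 0.114 | 88% | 93 |

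With k = 0.59 and 97.75 per arm, ρ of 0.3, 0.4 and 0.5 gives 83%, 85% and 87%.

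**Step 4: simulation.** In 800 simulated trials per setting (k = 0.73, ρ on the log-rate scale), power without and with the covariate was:
- ρ = 0.3: 82.4% and 83.3%
- ρ = 0.4: 82.0% and 86.1%
- ρ = 0.5: 83.1% and 89.0%.

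Each figure has a Monte Carlo standard error of about √(0.83 × 0.17/800) = 1.3 points. The direction matches the formula. The gain is about 1 point at 0.3 and 4 at 0.4, slightly below the formula's 3 and 5.

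A second simulation (600 trials per setting) let the covariate explain 10%, 20% or 30% of the overdispersion. The mean SE fell from 0.124 to 0.119, from 0.121 to 0.112 and from 0.120 to 0.106. The estimated log IRR stayed at about −0.36 with and without the covariate, so adjustment does not change what is being estimated.

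**Step 5: if 0.73 is the dispersion before fall-history adjustment.** Suppose, for illustration only, that fall history removes 30% of it. Then k = 0.511, the variance term is 0.405 + 1.022 = 1.426, SE = 0.111, and power is already 89%. Adding the score at ρ = 0.4 gives k = 0.511 × 0.84 = 0.429, SE = 0.105 and power of about 93%. The gain is about 3 points, against 5 in step 3.

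**The case against.** The strongest reply is that nothing here is wrong. Adjusting for fall history is valid, the sample size section claims 80% power without counting on the score, and an analysis plan that is not shown could still name it under the open clause. That stands as far as it goes: this is an improvement and not the correction of an error. It does not dispose of the point, because the article states a rule for the primary model, and a better rule is available from data already being collected.

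The size is also open to challenge, and this part stands in full. The document gives neither ρ nor k. The cohort finding concerns falls, with no strength given and no statement that the outcome was fall rate. This trial enrols only people who have fallen or are judged at risk, which may narrow the spread of the score. The score's description says that it includes the three factors, so it may hold other components too.

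Three stronger readings are tempting, but the document does not support them:

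- *The primary analysis is biased or invalid.* It is neither. The loss is one of efficiency.
- *The score will usually be dropped because it enters only when imbalanced.* The planned baseline t-tests make that reading plausible, but the text does not tie them to covariate selection and states no criterion, so no frequency can be given.
- *The trial is short of power without the score.* That needs a dispersion above 0.73. At 1.5, for example, the formula gives 54%, rising to 65% at ρ = 0.5. But 1.5 has no basis in the document and conflicts with its stated 80%.

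**Conclusion.** The point holds as a matter of efficiency and prespecification. The protocol identifies predictors of falls that act beyond past falls and measures a score that includes them before randomisation. It then leaves that score's entry into the primary model to a clause without a criterion.

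The direction of the gain is clear if the score predicts fall rate in this sample as the Background suggests. Its size is not derivable. The range of about 81% to 88% power rests on a two-sided test, a back-solved dispersion of 0.73 taken as what remains after fall-history adjustment, and an assumed ρ of 0.2 to 0.5. At ρ of 0.3 or less, only about 1 to 3 points are to be had, and less if fall history has yet to be taken out of the 0.73. The case for acting rests on the negligible cost and on removing a discretionary choice, more than on any particular power figure.

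**What to change.** In the Statistical analysis section, for the primary negative binomial model, replace the open clause on further confounders with: *and the baseline Parkinson's Disease Falls Risk Score, entered as a continuous covariate irrespective of observed baseline balance*. Add that models with further covariates are sensitivity analyses only. Do not add a provision to swap the score for its components if it proves collinear with fall history, because that would again let the data choose the primary model.

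The cost is one sentence before unblinding, one extra parameter among 230 participants, and a simple prespecified rule for a missing baseline score. No new data, visits or participants are needed.

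### Ordinal outcomes are compared by Mann-Whitney U with no baseline term, although a baseline score is collected for each: valid, but less precise than it need be

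*Protocol article*

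**What the plan says.** The Statistical analysis section of the protocol article treats two classes of secondary outcome differently.

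- Continuous outcomes: the between-group comparison of final values uses "General Linear Models (ANCOVA) controlled for pre-test performance".
- Ordinal outcomes: "Ordinally-scored data will be analysed for between group differences using the non-parametric Mann Whitney U statistic". The sentence names no baseline covariate and no time point. It comes directly after the sentence on t-tests of continuous baseline data.

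The Outcome measures section says that the secondary measures "will be collected on entry to the study and at the end of the 6-month intervention period by an assessor unaware of group allocation", and Measurements and Procedures likewise describes one pre-test and one post-test for all participants. A baseline score therefore exists for every secondary outcome.

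The Sample size section uses "a correlation between pre-and post measures of 0.7" when it derives the detectable differences for coordinated stability and knee extension strength. It gives no correlation for any other outcome. No section says which of the ten listed secondary outcomes count as ordinal.

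**The concern.** The plan uses the baseline value for one class of outcome and, as written, not for the other. A Mann-Whitney test on final scores takes no covariate, so the variation between participants that was already present at entry stays in the comparison as noise. In a chronic condition with stable differences between people, that share can be large.

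At stake is power for whichever secondary outcomes take this route. The Background names effects on risk factors for falls, physical abilities, fear of falling and quality of life as aims, and several of their measures are questionnaires or summed scores. If freezing, one of the three risk factors that the exercise targets, were scored as ordinal, it would be tested with less precision than balance and strength in the same trial. The Statistical analysis section fixes this method in so many words, so it is a stated choice and not a detail left to a fuller document.

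**Working it through.** **Inputs.** All are from the Sample size section: 115 per group, 15% dropout, two-sided 5% level, 80% power, pre-post correlation r = 0.7; balance mean 18 and SD 14; strength mean 16 kg and SD 6. Analysed per group: n = 115 × 0.85 = 97.75.

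**Step 1: reproduce the article's own figures.** With ANCOVA the residual SD is SD × √(1 − r²), and √(1 − 0.49) = 0.714. The detectable difference is (1.960 + 0.842) × residual SD × √(2/n), with √(2/97.75) = 0.143.

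- Balance: 2.802 × 14 × 0.714 × 0.143 = 4.01, and 4.01/18 = 22.3% (stated as 23%).
- Strength: 2.802 × 6 × 0.714 × 0.143 = 1.72 kg, and 1.72/16 = 10.7% (stated as 11%).

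Both agree after rounding up to the next whole percent, so these figures do rely on baseline adjustment. Without it the detectable differences would be 31.2% and 15.0%. At the stated differences power would fall from 82.5% to 54.3% (balance) and from 81.9% to 53.6% (strength). These two outcomes will in fact get ANCOVA; they only show what the adjustment is worth at r = 0.7.

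**Step 2: information kept without adjustment.** The variance of the comparison is proportional to SD² without adjustment and to SD² × (1 − r²) with it, so the share of information kept is 1 − r². An effect with 80% power under adjustment then has power Φ(2.802 × √(1 − r²) − 1.960). The values of r below are assumptions for ordinal scales.

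| r | information kept | loss | power instead of 80% |
|---|---|---|---|
| 0.5 | 0.75 | 25% | 68% |
| 0.6 | 0.64 | 36% | 61% |
| 0.7 | 0.51 | 49% | 52% |
| 0.8 | 0.36 | 64% | 39% |

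Under normality Mann-Whitney has a further efficiency factor of 3/π = 0.955 against a t-test. At r = 0.7 that gives 0.51 × 0.955 = 0.487 and power of about 50%.

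**Step 3: if change scores were tested.** Their variance is SD² × 2(1 − r). Relative to ANCOVA the information kept is (1 − r²)/[2(1 − r)] = (1 + r)/2. At r = 0.7 this is 0.85, a loss of 15%.

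**Step 4: check on ordinal data.** Scores with 13 levels were simulated, with 98 per arm and a shift of 0.29 SD on the underlying scale.

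| observed pre-post correlation | Mann-Whitney, final scores | rank ANCOVA | Mann-Whitney, change scores |
|---|---|---|---|
| about 0.71 | 49% | 79% | 72% |
| about 0.48 | 50% | 60% | 47% |

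With no true effect, and across 5-level and 13-level scores, all three methods rejected in about 5% of runs (4.0% to 5.8%, from 2,000 runs each). The difference is one of precision, not of validity.

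**The case against.** The strongest reply is that Mann-Whitney is a standard, valid test and that much of the apparent damage depends on things the article does not say. Several parts of this stand.

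- *Which outcomes are affected.* A reader might infer that the Freezing of Gait Questionnaire, the Falls Efficacy Scale, the Short Physical Performance Battery and the PANAS will go to Mann-Whitney. The article classifies none of them. Summed scores are often analysed as continuous, and then they would get ANCOVA.
- *Size.* A reader might carry r = 0.7 over and take a loss of half as fact. The article gives that value for two continuous measures only. At a correlation near 0.5 the gap is modest.
- *What is compared.* The sentence names no time point. It could mean final scores, change scores or, given its position, baseline comparisons.
- *Effect estimate.* A reader might infer that the test can give only a p-value. It cannot be faulted for that: U divided by the product of the group sizes estimates the probability of superiority, and a Hodges-Lehmann shift with its interval can accompany it. That a condensed article names no effect measure is not an error in itself.
- *Bias.* A reader might infer that chance baseline imbalance invalidates the result. Allocation is random and the type I error already allows for such imbalance.
- *Stratum.* The ANCOVA sentence names only pre-test performance, so omitting the falls-history stratum does not set the ordinal route apart.

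What does not stand is that nothing need change. If final scores are meant, collected information is discarded. If change scores are meant, the text should say so, and some information is still lost. If only baseline comparisons are meant, the article states no outcome analysis for ordinal measures.

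**Conclusion.** The point holds as one about precision in secondary outcomes. As written, ordinal outcomes are compared without their baseline score, while continuous outcomes are adjusted for theirs. Relative to a baseline-adjusted analysis of final scores, the loss of information is about 25% at a pre-post correlation of 0.5, about half at 0.7 and 64% at 0.8; at 0.7 it is about 15% if change scores are tested. These figures rest on an assumed correlation for ordinal scales and on a normal approximation, which the simulation supports.

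The documents do not support a firm figure for any named questionnaire, a claim of bias, or a claim that no effect estimate can be had. The number of outcomes affected is unknown, and the primary comparison of fall rates is not touched. The change is worth making because the data are already collected and the cost is small.

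**What to change.** In the Statistical analysis section, replace the Mann-Whitney sentence so that it does three things.

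1. List the secondary outcomes treated as ordinal; all others follow the ANCOVA route.
2. Analyse final scores of the listed outcomes with a proportional-odds model, or rank ANCOVA for long scales, with treatment, baseline score and the falls-history stratum from the Randomization section as terms.
3. Report an effect estimate with 95% CI: the odds ratio for the proportional-odds model, or for rank ANCOVA a stated measure such as the probability of superiority or a Hodges-Lehmann shift. Keep Mann-Whitney as a sensitivity check.

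If the existing sentence was meant for baseline comparisons or change scores, say so. The cost is a sentence or two, with no new data and no change to the sample size. The small downside is that the proportional-odds assumption must be checked.
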